## SUMMARY

**Rationale:** Achalasia is a rare motility disorder of the esophagus that is characterised by aperistalsis of the esophageal body and dysrelaxation of the lower esophageal sphincter (LES). Current treatment is palliative and the aim of the treatment is to diminish the obstructive function of the esophagogastric junction (EGJ). Due to this approach the most frequent complication post-treatment is gastroesophageal reflux (GER). However, not every treated patient develops GER symptoms and the mechanism behind the occurrence of GER in treated achalasia are unclear.

**Objective:** To investigate the underlying mechanisms of gastroesophageal reflux and gastroesophageal reflux symptoms in treated achalasia patients.

**Study design:** A prospective observational study.

**Study population:** Treated achalasia patients with and without gastroesophageal reflux symptoms visiting the outpatient clinic of the Gastroenterology Department.

**Main study parameters/endpoints:**

*Primary:*

- Gastroesophageal reflux episodes

*Secondary:*

- LES pressure
- Esophagogastric junction distensibility
- Sensitivity to acid perfusion and distension
- Level of esophageal stasis
- Width/diameter of the esophagus.

**Nature and extent of the burden and risks associated with participation, benefit and group relatedness:**

Five different measurements will be performed in two subsequent days. Study subjects will undergo an EndoFLIP, an acid perfusion test, combined high-resolution manometry (HRM) and pH-impedance monitoring and finally a timed barium esophagography will be performed. At the beginning of the study participants will be asked to fill in questionnaires. The measurements are standard procedures that are routinely performed at the motility centre of the Gastroenterology department in the evaluation of achalasia patients. The associated complications are minimal. Study subjects will receive 150 euro for study participation, to cover work day loss. The study will give insight in the mechanisms behind GER-related symptoms which is important for the management of these symptoms and potentially have consequences for the choice of the initial treatment for achalasia.

## 1. INTRODUCTION AND RATIONALE

### *Achalasia*

Achalasia is a rare motility disorder of the esophagus with an annual incidence of 1 per 100.000 persons. Achalasia is characterised by aperistalsis of the esophageal body and dysrelaxation of the lower esophageal sphincter (LES) caused by progressive destruction and degeneration of the neurons in the myenteric plexus. This leads to subsequent retention of food and saliva in the esophagus, resulting in the typical symptoms of achalasia such as dysphagia, chest pain, regurgitation of undigested food and weight loss. Diagnosis is currently based on typical manometric findings; incomplete relaxation of the LES upon deglutition, absence or simultaneous esophageal contractions and often a hypertensive LES. Due to a lack of knowledge on the cause of the disease, the treatment of achalasia is currently purely palliative and focused on symptom relief. The aim of the treatment is to destroy the occluding function of the esophagogastric junction using endoscopic balloon dilatation, surgical Heller myotomy or per-oral endoscopic myotomy (POEM). The therapeutic success of these three treatments is comparable but all have a risk of complications. The most frequent complication post-treatment is gastroesophageal reflux (GER). This is not surprising because the occluding function of the esophagogastric junction is destroyed and thereby the mechanism that protects the esophagus against reflux of gastric content is compromised. The incidence of GER varies and is dependent on the type of treatment; 15%-33% in pneumodilatation, 31.5% in Heller myotomy without fundoplication compared to 8.8%-23% in Heller myotomy with fundoplication.

### *GER in treated achalasia*

Achalasia and gastroesophageal reflux disease (GERD) are generally thought to represent opposite ends of the spectrum of esophageal sphincter dysfunction. In achalasia there is dysrelaxation of the LES. But in GERD the LES is hypotonic or undergoes frequent relaxations which lead to an abundant exposure of the esophagus to gastric components. Typical symptoms of GERD are heartburn, chest pain and/or regurgitation. However, these symptoms are also described in patients with achalasia, in both untreated and treated patients. In untreated achalasia symptoms of GER would be expected to be rare because the esophageal sphincter is tightly closed. However studies have described variations in LES pressure during the day in achalasia patients and also transient LES relaxations (TLERs) which could lead to the exposure of gastric components in the esophagus and cause reflux symptoms.

In treated achalasia the esophagogastric junction is destroyed and thereby treated patients seem to be more susceptible for GER. The mechanisms behind the occurrence of GER symptoms in treated achalasia are unclear. It is hypothesized that these symptoms can be caused by true GERD or by retention and fermentation of retained food in the esophagus due to the impaired esophageal peristalsis. Several studies, as mentioned before have described that true GERD can occur in achalasia patients as a result of transient relaxations of the LES (TLESRs). Furthermore after treatment it is suggested that true GERD occurs in patients with a lower mean LES pressure post-treatment. However, other studies contradict these findings. To distinguish GERD from fermentation a 24-hour combined multichannel intraluminal impedance and pH monitoring can be used. With these methods reflux episodes can be discriminated from periods where there is stasis of food.

Previous studies that investigated GER after pneumodilation or Heller myotomy showed that in a substantial proportion of patients there is discordance between GER symptoms and the results of reflux monitoring. Furthermore the studies show considerable variability in the incidence of GER symptoms. At this moment it is unclear why there is a discrepancy in the degree and severity of GER symptoms between treated patients. Additionally the exact mechanism behind these symptoms stays indistinct. It could be due to true GERD or fermentation of food. Furthermore, variability in pain sensitivity or in esophageal distensibility could play a role, in which an impaired distensibility could cause more stasis and symptoms. A better insight in the underlying mechanism of GER symptoms in treated achalasia is important because it could influence the choice of the initial treatment.

In conclusion, post-treatment, patients with achalasia often describe reflux-like symptoms. So far there is no convincing evidence that these symptoms are really caused by GERD. Understanding the mechanism behind GER-related symptoms is important for further treatment of these symptoms and could have consequences for the choice of the initial treatment for achalasia.

## 2. OBJECTIVES

Our hypothesis is that gastroesophageal reflux symptoms in treated patients with achalasia are dependent on retention and fermentation of food due to a reduced clearance by aperistalsis of the esophageal body rather than the result of true acid reflux episodes. We expect a difference in gastroesophageal reflux episodes, LES pressure, sensitivity to acid and esophageal distension in the treated patients with achalasia that experience

**Protocol ID NL42367.018.12****Reflux symptoms in achalasia**

gastroesophageal reflux symptoms compared to the group that does not encounter gastroesophageal reflux symptoms.

Based on the hypothesis the following study objective is formulated.

Primary objective:

- To investigate the underlying mechanisms of gastroesophageal reflux and gastroesophageal reflux symptoms in treated achalasia patients.

### **3. STUDY DESIGN**

This observational study has a prospective design. Two groups of study subjects will be included. Treated patients with achalasia with gastroesophageal reflux symptoms and treated patients with achalasia without gastroesophageal reflux symptoms. On baseline, clinical data will be collected regarding medical history, family history and medical symptoms related to GER or achalasia.

In all the included study subjects five different measurements will be performed in two days, as outlined in the schematic overview under subheading 5.2.1 'research protocol'. The measurements will take place in the AMC at the outpatient clinic of the Motility Centre of the Gastroenterology Department. The duration of the study is dependent on the rate of inclusion of the study subjects but, it is expected that in two years all study subjects will be included.

### **4. STUDY POPULATION**

#### **4.1 Population (base) and study enrolment**

Patients that visit the outpatient clinic of the Motility Centre of the Gastroenterology Department of the AMC will be approached by the physician of the patient. In case patients are interested to participate the coordinating investigators of the study will provide further information about the study.

Patients should be diagnosed with achalasia by manometry using the predefined manometric criteria and all underwent previous treatment for achalasia. Eligible patients will be given a verbal explanation of the study. Each patient will receive a patient information brochure about the study and an informed consent form for participation. Patients will be given sufficient time to read the information and ask questions. Before any study procedures are initiated the patient must sign the informed consent form.

**Protocol ID NL42367.018.12****Reflux symptoms in achalasia**

The annual incidence of achalasia is 1 per 100.000 persons. In the Netherlands a substantial proportion of the patients with achalasia are followed at the Motility Centre of the AMC. The number of patients visiting our department is sufficiently high to find participants for the study.

**4.2 Inclusion criteria****4.2.1 Treated achalasia patients with gastroesophageal reflux symptoms**

- Diagnosis of idiopathic achalasia confirmed by esophageal manometry that shows the following criteria:
  - Aperistalsis or simultaneous contractions in the esophageal body.
  - LES dysrelaxation.
- Treatment of achalasia with one of the following procedures:
  - Endoscopic balloon dilatation
  - Surgical Heller myotomy
  - per-oral endoscopic myotomy (POEM)
- Minimum total score on the GastroEsophageal Reflux Disease Questionnaire (GERDQ) of  $\geq 8$ .
- Gastroesophageal symptoms after treatment lasting more than 3 months.
- Age 18-80 years.
- Written informed consent.

**4.2.2 Treated achalasia patients without gastroesophageal reflux symptoms**

- Diagnosis of idiopathic achalasia confirmed by esophageal manometry that shows the following criteria:
  - Aperistalsis or simultaneous contractions in the oesophageal body.
  - LES dysrelaxation.
- Treatment of achalasia with one of the following procedures:
  - Endoscopic balloon dilatation
  - Surgical Heller myotomy
  - per-oral endoscopic myotomy (POEM)
- Maximum total score on the GastroEsophageal Reflux Disease Questionnaire (GERDQ) of  $< 8$ .
- No gastroesophageal symptoms after treatment.
- Age 18-80 years.
- Written informed consent.

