## 8. STATISTICAL ANALYSIS

Statistical analysis will be performed in collaboration with the department of Biostatistics and Epidemiology of the University of Amsterdam. After testing for normality, unpaired testing will be performed between the two treatment groups for all primary and secondary outcome parameters. Categorical variables will be compared using the Chi-square test. Comparison of the numerical variables will be dependent of the distribution of the data.

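### Section 4.2.2 sets no minimum time since treatment for symptom-free patients, while 4.2.1 implies more than three months for symptomatic ones

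*Protocol*

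**What the plan says.** The study compares treated achalasia patients with and without reflux symptoms (Protocol sections 2 and 3), with a target of 20 per group (section 4.4).

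- **Symptomatic group (4.2.1).** GERDQ total of 8 or more, and "Gastroesophageal symptoms after treatment lasting more than 3 months".
- **Symptom-free group (4.2.2).** GERDQ total below 8, and "No gastroesophageal symptoms after treatment". No interval since treatment is given.
- **Exclusions (4.3).** The list is the same for both groups and does not mention time since treatment.
- **Prior procedure.** Both groups carry the same entry, "Treatment of achalasia with one of the following procedures", followed by balloon dilatation, Heller myotomy and POEM. Fundoplication is not mentioned there. Section 1 says that the frequency of GER depends on the procedure. It gives a range of 15% to 33% for dilatation and, for surgery, "31.5% in Heller myotomy without fundoplication compared to 8.8%-23% in Heller myotomy with fundoplication".
- **Analysis (section 8).** After a check for normality, "unpaired testing will be performed between the two treatment groups for all primary and secondary outcome parameters". A chi-square test is named for the categorical ones.

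**The concern.** The label symptom-free means little without a minimum period in which symptoms could have appeared. A patient seen three weeks after treatment without reflux symptoms has shown only that none arose in three weeks. Such a patient may go on to meet 4.2.1, yet would be counted for good in the comparison group.

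The groups may also differ in how long ago they were treated, a difference created by the eligibility rules and not by reflux symptoms. Lower esophageal sphincter pressure, junction distensibility, stasis and reflux episodes are all measured after treatment. Any dependence of these on the interval since treatment would be mixed into the comparison of the symptom groups.

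**Working it through.** **Step 1. Who can enter, by interval since a first treatment** (all other criteria met):

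| Time since treatment | Reflux symptoms now | Symptomatic group | Symptom-free group |
|---|---|---|---|
| 3 weeks | none, GERDQ below 8 | no | yes |
| 3 weeks | present, GERDQ 8 or more | no, duration too short | no |
| over 3 months | none, GERDQ below 8 | no | yes |
| over 3 months | present for over 3 months, GERDQ 8 or more | yes | no |

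In the first three months after treatment, enrolment is open to one group only. The table uses a first treatment because neither section says which treatment counts when a patient has had several. For a retreated patient, the implied interval runs from the last treatment only if that is the one meant in 4.2.1.

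**Step 2. Can the analysis repair it?** Not by adjustment. No symptomatic patient exists at intervals of three months or less, so a model term for time since treatment would have to extrapolate there. The recently treated patients could be dropped, but section 4.4 requires 19 per group and plans 20, so the margin is one patient per group.

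That requirement itself is sound. With 30% and 75%, two-sided 5% and 80% power, the mean proportion is 0.525 and

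n = [1.960 × √(2 × 0.525 × 0.475) + 0.842 × √(0.30 × 0.70 + 0.75 × 0.25)]² / 0.45² = (1.384 + 0.531)² / 0.2025 = 18.1, rounded up to 19.

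The protocol's figure is reproduced (uncorrected chi-square), so the concern is not about the sample size.

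**Step 3. Size of the time effect.** A figure would need the share of symptom-free patients treated within three months, and either the change in the measurements over that period or the share who later develop symptoms. The protocol gives none of these. The two mechanisms need not point the same way: future cases in the comparison group would tend to make the groups alike, while a short-lived effect of recent treatment could drive them apart.

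**Step 4. Prior procedure, for scale only.** Section 1 gives 31.5% GER after Heller without fundoplication and 8.8% to 23% with it. Assume that 60% of one group and 30% of the other had no fundoplication, with no true association with symptoms. The spurious difference is (0.60 − 0.30) × (rate without − rate with):

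- with 8.8%: 0.30 × (0.315 − 0.088) = 0.068, or 6.8 points;
- with 23%: 0.30 × (0.315 − 0.23) = 0.0255, or 2.6 points.

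The split is assumed, and these rates are for GER, whereas section 4.4 counts episodes from GER or fermentation.

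**The case against.** The three-month rule in 4.2.1 is a symptom-duration criterion. It has no natural counterpart in patients without symptoms, and the interval since treatment is only implied. Nothing in the protocol suggests that many recently treated patients would be enrolled. Both statements are right. They limit how much the gap is likely to matter but do not close it, because 4.2.2 as written admits these patients and 4.2.1 does not.

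A reader might infer four stronger things that the document does not support.

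- *That recently treated symptom-free patients would look better on pressure, distensibility and stasis.* The protocol gives no time course for any of these, so the direction is unknown.
- *That prior procedure confounds every comparison and must be stratified for.* Section 1 does say that GER incidence depends on procedure. But treatment works by weakening the junction, so procedure may act through the very quantities being measured, and stratifying could then remove variation that the study wants to see. With 20 per group and three procedures, strata would average 20/3, or about 6.7, patients per group. Such choices are commonly left to a statistical analysis plan, which is not shown here.
- *That procedure mix could explain half of the 45-point target.* That takes complete separation of the groups by fundoplication and the lowest rate in the range: 31.5 − 8.8 = 22.7 points. At 23% even complete separation gives 31.5 − 23 = 8.5 points.
- *That section 8 leaves the contrast undefined.* Its reference to treatment groups is a slip. Sections 2, 3 and 4.4 all state the comparison by symptoms.

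**Conclusion.** The point holds as an eligibility asymmetry. A patient first treated within the last three months can enter the symptom-free group and cannot enter the symptomatic one. The groups can therefore differ in time since treatment, and some symptom-free patients may be future cases. This rests on the wording of 4.2.1, 4.2.2 and 4.3 alone; for patients treated more than once it also assumes that the last treatment is the one meant. Neither the size nor the direction of the bias can be derived from the document.

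The gap deserves correction because it is a matter of who is enrolled, which a later analysis plan can handle only by discarding patients. It does not show that the planned comparisons are invalid. The 2.6 to 6.8 points for procedure mix are a separate illustration under an assumed split; they justify describing the groups by procedure, not requiring a stratified primary analysis.

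**What to change.** - **Section 4.2.2:** add a minimum of more than three months since the last treatment, matching what 4.2.1 implies. State in 4.2.1 as well that the last treatment is meant. Cost: one line in each section, and a few recently treated patients wait before they can enter as symptom-free.
- **Reporting:** give time since last treatment and prior procedure, including whether fundoplication was done, for each group. Section 3 already collects medical history at baseline, so this may need no new data item.
- **Section 8:** replace the word treatment by symptom in the description of the two groups. This is editorial.
- **Optional:** an analysis stratified by procedure, in two or three levels, as a sensitivity analysis beside the crude result. Cost: thin strata and lower precision, and it must be read with the caution that procedure may act through the measured mechanisms.

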### 4.3 Exclusion criteria

#### 4.3.1 Treated achalasia patients with gastroesophageal reflux symptoms

- Pseudoachalasia.
- Upper gastrointestinal malignancy.
- Chagas disease.
- Peptic ulcer disease.
- Inability to stop PPI, H2-receptor antagonist or prokinetic drug for two weeks
- Presence of an extremely dilated oesophagus body >5 cm

#### 4.3.2 Treated achalasia patients without gastroesophageal reflux symptoms

- Similar to 4.3.1

### 4.4 Sample size

Treated achalasia patients with or without gastroesophageal reflux symptoms will be included. Per group we aim to include 20 study subjects. In the literature the incidence of GER symptoms in patients with achalasia post-treatment is very variable. Articles describe an incidence that differs between 10% up till 60%. This variability in the incidence is probably caused by the different diagnostic approaches in these studies. Furthermore the GER symptoms do not always correlate with a positive pH-impedance monitoring for GERD or fermentation of food.

Based on this we expect that 30% of the patients without GER symptoms will have gastroesophageal reflux episodes caused by GER or fermentation of food. For the patients with GER symptoms we estimate that in 75% gastroesophageal reflux episodes occur caused by GER or fermentation. We consider a 45% difference in gastroesophageal reflux episodes between the two groups as clinically relevant. When, using a two-group chi-square test with a two-sided significance level of 5% and a power of 80%, the sample size required in each group is 19 subjects. Based on this we aim to include 40 study subjects. Below we have calculated the sample sizes based on our main secondary study parameters to show that with a sample size of 40 study subjects it is possible to attain these secondary study parameters.

We believe that the three main secondary study parameters are LES pressure, esophagogastric junction distensibility and the level of esophageal stasis. Several studies have described that true GERD occurs in patients with a lower mean LES pressure post-treatment. However, other studies contradict these findings. Based on our hypothesis we believe that patients with GER symptoms have a higher mean LES pressure post-treatment

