**5. METHODS****5.1 Study parameters****5.1.1 Primary study parameter**

- Gastroesophageal reflux episodes

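### The powered primary endpoint pools true reflux and fermentation, so a significant result cannot by itself tell the study hypothesis from its rival

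*Protocol*

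**What the plan says.** Section 2 of the protocol sets two explanations against each other. Symptoms are hypothesised to depend on retained, fermenting food "rather than the result of true acid reflux episodes".

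Sections 5.1.1 and the Summary name the primary parameter only as "Gastroesophageal reflux episodes", with no cause attached. Section 4.4 is the one place that turns it into a quantity with expected rates, and there the two causes are joined. For the group without symptoms: "we expect that 30% of the patients without GER symptoms will have gastroesophageal reflux episodes caused by GER or fermentation of food". For the other group: "For the patients with GER symptoms we estimate that in 75% gastroesophageal reflux episodes occur caused by GER or fermentation". The 45-point difference is tested by a two-sided 5% chi-square test with 80% power, giving 19 per group; 20 per group are planned.

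Section 5.2.2, on analysis of the manometry and pH-impedance data, treats the causes as distinguishable. It gives one pattern for true reflux (sphincter relaxation, retrograde impedance fall, abrupt pH drop, then recovery) and another for fermentation (a slower, longer fall in both). Section 8 plans unpaired comparisons of the listed parameters between the two groups. No cause-specific episode endpoint, expected rate or powered comparison is stated.

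**The concern.** The hypothesis is of the form A rather than B, and the event that carries the sample size is A or B. If fermentation drives symptoms, the symptomatic group has more pooled events. If true reflux drives them, it also has more pooled events. A significant primary result would be welcome under either account and would favour neither.

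This matters because the protocol says, in the Summary and in sections 1 and 9.3, that the findings might influence the choice of initial treatment for achalasia. A significant pooled result could be cited in support of either mechanism. A reader could also take the 80% power in section 4.4 to apply to the fermentation hypothesis, when it applies only to the pooled event.

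**Working it through.** **Inputs from section 4.4:** pooled event 30% v 75%; two-sided 5%; 80% power; 19 per group required, 20 planned. The division of the 30% and the 75% by cause is not given, so every split below is an assumption.

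**1. The stated sample size.** Chi-square with pooled variance under the null and no continuity correction:

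n = [1.960·√(2·p̄·q̄) + 0.842·√(p₁q₁ + p₂q₂)]² / (p₂ − p₁)², with p̄ = (0.30 + 0.75)/2 = 0.525.

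- 1.960·√(2 × 0.525 × 0.475) = 1.960 × 0.706 = 1.384
- 0.842·√(0.21 + 0.1875) = 0.842 × 0.630 = 0.531
- n = (1.384 + 0.531)² / 0.45² = 3.666 / 0.2025 = 18.1, rounded up to 19

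The stated figure is reproduced. Power is 82.0% at 19 per group and 84.1% at 20 (82.3% at 20 by exact enumeration of the uncorrected chi-square).

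**2. Opposite mechanisms, same composite.** First let the two causes occur independently within a patient, so that pooled rate = 1 − (1 − GER)(1 − fermentation):

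- No symptoms, GER 10%, fermentation 22%: 1 − 0.90 × 0.78 = 29.8%
- Symptoms, only GER raised (68%, 22%): 1 − 0.32 × 0.78 = 75.0%
- Symptoms, only fermentation raised (10%, 72%): 1 − 0.90 × 0.28 = 74.8%

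Next assign each positive patient one cause, with the no-symptom group at 15% fermentation and 15% GER:

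| Symptomatic group | Pooled | Pooled power, n = 20 | Fermentation alone | Power, n = 20 |
|---|---|---|---|---|
| 60% fermentation, 15% GER | 30% v 75% | 84.1% | 15% v 60% | 86.6% |
| 37.5% of each | 30% v 75% | 84.1% | 15% v 37.5% | 36.1% |
| 15% fermentation, 60% GER | 30% v 75% | 84.1% | 15% v 15% | no difference to detect |

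The pooled columns are identical in all three rows.

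**3. What the planned size gives for fermentation alone.** Suppose fermentation is the same share of events in both groups:

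| Share | Fermentation rates | Power, n = 20 | n per group for 80% |
|---|---|---|---|
| 0.90 | 27.0% v 67.5% | 74.6% | 23 |
| 0.75 | 22.5% v 56.25% | 59.5% | 32 |
| 0.50 | 15.0% v 37.5% | 36.1% | 59 |
| 0.25 | 7.5% v 18.75% | 17.9% | 141 |

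Across the splits in steps 2 and 3 that contain a fermentation difference, power runs from 17.9% to 86.6%.

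**4. Why absence of a true-reflux difference cannot be read from a p-value.** With 20 per group and an assumed true-reflux rate near 30% in both groups, the 95% CI half-width is 1.96·√(2 × 0.3 × 0.7/20) = 0.284, about 28 points. At 15% in both it is 1.96·√(2 × 0.15 × 0.85/20) = 0.221, about 22 points. A non-significant result leaves large differences open.

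**The case against.** The strongest reply is that the study contains more than its pooled test. Section 5.2.2 gives a pattern for each cause, has observers blinded to patient characteristics, and plans to correlate symptoms with acid and non-acid episodes in a two-minute window, which bears on whether true reflux produces the symptoms. Section 4.4 also sizes three secondary comparisons (sphincter pressure 18, distensibility 12, stasis 17 per group), each with a direction predicted from the fermentation hypothesis. The pooling appears only in section 4.4, and nothing forbids a cause-specific analysis. All of this stands. A reader might infer that the study cannot answer its own question; the documents do not support that. They support the narrower statement that the powered primary test cannot.

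A reader might also infer that the sphincter-pressure comparison fails for the same reason, since section 4.4 reports studies in which "true GERD occurs in patients with a lower mean LES pressure post-treatment" and then says "we believe that patients with GER symptoms have a higher mean LES pressure post-treatment", so that a mixed symptomatic group would show opposing effects that cancel. This goes too far. The same section says at once that other studies disagree. It gives neither the share of true-reflux patients among the symptomatic nor their mean pressure, so any loss of power would rest on invented inputs. A mixture would in general dilute the difference, not abolish it. The protocol nowhere ties true reflux to greater distensibility, so the argument does not extend to that measure.

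Finally, one might fault the absence of a model relating pressure, distensibility and stasis to reflux itself. That kind of detail is commonly left to a statistical analysis plan, which is not at hand, and its absence here is not an error.

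What the reply does not remove is that the only expected rates and the only power statement for the primary endpoint concern the pooled event.

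**Conclusion.** The point holds in its narrow form. As section 4.4 stands, a significant primary result is equally compatible with the hypothesis in section 2 and with its rival. This follows from the definition of the event and needs no particular split by cause; the splits only illustrate it. The 19 per group is correct for the composite and for nothing else. For fermentation alone, power at 20 per group is anywhere from about 18% to 87% under the illustrative splits, which assume either a 15% base rate for each cause or a constant fermentation share, with one cause per positive patient.

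A difference in fermentation would not be sufficient by itself either. The hypothesis says fermentation rather than true reflux, so the true-reflux difference and its precision have to be read alongside it.

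**What to change.** In sections 5.1.1 and 4.4:

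1. Define two per-patient components, true reflux episodes and fermentation episodes, using the patterns in section 5.2.2. Say that a patient may count in both. Because the manometry catheter comes out after the first hours, say also how episodes in the remaining pH-impedance recording are classified.
2. Compare each component between the symptom groups, giving the difference and its 95% CI, alongside the composite. The composite need not be demoted.
3. State that the composite alone does not support the hypothesis. Support requires a higher fermentation rate in the symptomatic group, read together with the CI for the true-reflux difference and not with its non-significance.
4. Restate that 19 per group gives 80% power for the composite only, and that power for either component depends on a split that is not known in advance.

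The cost is wording and two further comparisons, which may have low power at 20 per group. No additional procedures or data are needed. If the sponsor wants the fermentation contrast itself to be powered, an expected rate by cause must be stated, and the required number could exceed 20 per group.
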